**Secondary Outcome:**

Mean birth weight and gestational age at birth and the frequencies of resuscitation, NICU admission, and death

fetal or within the first 12 hours. These results will be controlled by the beginning of prenatal follow-up, maternal age, and weight gain.

gestational.

**Sample Size in Brazil:** 80

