**Proposed Methodology:**

This is a cohort study with a convenience sample of normotensive and hypertensive pregnant women followed at the prenatal clinic and in the IFF/Fiocruz pregnant women's ward. The prenatal service at the IFF “takes care of pregnant women with a gestational age of less than 24 weeks, without clinical comorbidities and with indications such as infectious diseases with risk of fetal repercussion, adolescents aged Fifteen years, history of previous malformation pregnancies, maternal age 35 years or older, multiple gestations, hemolytic disease perinatal, and maternal gynecological malformation. "The services will take place at the Fernandes Figueira Institute, a unit of the Oswaldo Cruz Foundation dedicated to teaching, research, and technological development. The Institute is recognized as a reference center for the health of women, children, and adolescents. It has the “MS assignment of assisting, coordinating and evaluating actions aimed at women's and children's health within the scope of national." The research will be composed of two groups: a control group formed by normotensive pregnant women and an exposed group of pregnant women hypertensive. The appointments will take place on Tuesdays and Thursdays at the prenatal outpatient clinic or the pregnant women's ward of the IFF, with all pregnant women who agree to participate in the research. These will be met with OMT from their entry into the study until the time of termination of pregnancy. OMT consultations will occur at each routine visit of these pregnant women to the outpatient clinic. Pregnant women will respond to a standard form prepared by the researchers in addition to a life questionnaire, the SF-36, applied after each meeting. The average duration of consultations takes around 30 to 40 minutes, and the techniques chosen are widely recognized by osteopathic professionals and described in articles as safe practices. There will be no maneuvers on the patient's abdomen, just as there will be no maneuvers on the viscera, as it is not a practice of visceral osteopathy. Before and after each visit, the BP of the pregnant woman will be evaluated using a blood pressure device. OMRON HEM-7320F, validated for research by the Brazilian College of Cardiology1F. BP will always be measured on the left arm, with the patient sitting and in left lateral decubitus. Pregnant women who are hospitalized in the ward, they will also be treated with the same OMT but will have a different measurement. Before the OMT observes, the data of blood pressure (BP), heart rate (HR), and respiratory rate (RR) are present in the electronic monitor (without any interference by the human operator). An ultrasound (US) will be performed for fetal evaluation through the doppler of the uterine, umbilical and cerebral arteries, and then the same life questionnaire (QoL) will be applied. Only after these measurements will OMT occur. After 30 minutes of the intervention, the blood pressure, heart rate, and respiratory rate data on the electronic monitor will be measured again (without interference from the human operator). A new ultrasound will be performed for fetal evaluation through the doppler of the uterine, umbilical and cerebral arteries. One recent evaluation will be carried out 24 hours after OMT. Blood pressure, heart rate, and respiratory data will again be observed on the electronic display (without any interference by the human operator). Another ultrasound will be performed for fetal evaluation through the doppler of the uterine, umbilical and cerebral arteries, and then the same life questionnaire will be applied. The OMT protocol includes techniques for balance ligament (BLT), myofascial, muscular energy, and cranial tensions. High-velocity and low-speed (HVBA) styles were excluded. Pregnant women in both groups will maintain standard obstetric and drug treatment and must sign a free-term consent, their willingness, and awareness of participating in the research.

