
**Inclusion Criteria:**

**Inclusion criteria:** the sample from normotensive and hypertensive pregnant women in the third trimester, over 18 years old, and accepted at the IFF/Fiocruz to carry out prenatal care at the outpatient clinic and in the pregnant women's ward from July 2021 to September 2022. The minimum age of patients was defined according to the physiological differences observed between adolescent and adult pregnant women.

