**Data Analysis Methodology:**

Relative risk (RR) and differences in means will be the measures of association used to assess the relationship between BMT and changes in hemodynamics as well as fetal outcomes. Categorical variables will be evaluated using the chi-frame test and numeric variables using the t-student test. The data will be digitized in the database with the help of Epi INFO and analyzed in SPSF

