**Details:**

Clinical and demographic data of the pregnant women will be observed (age, education, professional situation, ethnicity, smoking, alcoholism, number of children, number of pregnancies, number of abortions, number of births, the practice of physical activities, BMI at the beginning of pregnancy); obstetrics (date of last menstruation, diabetes, kidney pathologies, chronic respiratory pathologies, musculoskeletal pain, cardiac pathologies, diseases autoimmune disorders, a medication used, infection, gestational weight gain, abdominal pain, bleeding); maternal hemodynamics (blood pressure diastolic, systolic blood pressure, and heart rate); and perinatal (ruptured pouch, membrane rupture, chorioamnionitis, meconium, type of delivery, fetal death, birth weight, gestational age, weight-for-age adequacy, head circumference, length, weight z-score, weight z-score length, HC z-score, 1st, and 5th-minute Apgar, resuscitation, admission to the neonatal ICU, and death within the first 12 hours).will be observed from the medical records at each consultation of the patients in the prenatal clinic and recorded in a specific clinical history of the study for subsequent registration in the database.

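### Birth outcomes are to be controlled for gestational weight gain with no time point, without gestational age at enrolment or early-pregnancy BMI, and by tests that cannot adjust

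*Protocol*

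**What the plan says.** The Protocol, Secondary Outcome, lists "Mean birth weight and gestational age at birth and the frequencies of resuscitation, NICU admission, and death" (fetal, or within the first 12 hours). It then says "These results will be controlled by the beginning of prenatal follow-up, maternal age, and weight gain", and the next word marks the gain as gestational. No cut-off for that gain is given there. Under Details, it is one of the items taken from the medical records at each consultation.

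The Data Analysis Methodology section says "Relative risk (RR) and differences in means will be the measures of association", to be used for the relation between the manual treatment and haemodynamics and fetal outcomes. It adds "Categorical variables will be evaluated using the chi-frame test and numeric variables using the t-student test". No regression, covariance or stratified method is named.

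Under Proposed Methodology the groups are "a control group formed by normotensive pregnant women and an exposed group of pregnant women hypertensive". All participants receive OMT from study entry to the end of pregnancy. The same section says the prenatal service "takes care of pregnant women with a gestational age of less than 24 weeks", whereas Inclusion Criteria take "normotensive and hypertensive pregnant women in the third trimester". Details also lists "BMI at the beginning of pregnancy", the date of last menstruation and a weight z-score.

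**The concern.** A covariate used to control confounding should not be affected by the exposure or by the outcome. Gestational weight gain with no cut-off can fail on both counts. In women with chronic hypertension, all of it follows the exposure. In gestational hypertension, which the Introduction dates from week 20, the later part does. Whatever is gained after third-trimester entry also follows the start of OMT. Gain carried on towards delivery is larger when pregnancy lasts longer and includes the baby, so gestational age at birth and birth weight feed back into their own covariate.

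Two useful controls are absent. A woman cannot deliver before the week in which she enrols, so gestational age at birth is observed only from enrolment onward, and start of prenatal care does not measure that point. Early-pregnancy BMI is recorded but not used, although the groups are a convenience sample defined by hypertension status. Finally, a two-sample t test and a plain chi-square test adjust for nothing, so the two sections do not fit together. At stake is whether the secondary birth results can be read at all, and whether the adjusted result depends on a choice made after the data are seen.

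**Working it through.** **1. The plan's own figure.** The only design number is a sample size of 80. No alpha, power, SD, effect size or group split is given, so it cannot be reproduced, and it is not in dispute here. A 40:40 split is assumed below.

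**2. Birth weight: formula and inputs.** The protocol gives no figures, so all inputs are assumed:
- within-group SD of birth weight: s = 0.5 kg
- SD of the rest of the weight gain: u = 4.5 kg
- correlation of that rest with birth weight within group: r = 0, 0.2 or 0.4
- difference in the rest of the gain, hypertensive minus normotensive: m = −2, 0 or +2 kg
- true group difference in birth weight: T = −200 g or 0

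Total gain is the rest plus birth weight. The within-group slope of birth weight on total gain is g = (s² + r·s·u) / (u² + s² + 2·r·s·u), and the adjusted difference is T − g·(m + T).

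- r = 0: g = 0.25/20.5 = 0.0122, or 12.2 g per kg
- r = 0.2: g = 0.70/21.4 = 0.0327, or 32.7 g per kg
- r = 0.4: g = 1.15/22.3 = 0.0516, or 51.6 g per kg

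Adjusted difference (g) when the true difference is −200 g:

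| r | m = −2 kg | m = 0 | m = +2 kg |
|---|---|---|---|
| 0 | −173 | −198 | −222 |
| 0.2 | −128 | −193 | −259 |
| 0.4 | −87 | −190 | −293 |

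The cell r = 0, m = 0 isolates the fetus being part of the gain: a 2 g shift. The largest shifts are +113 g and −93 g. With T = 0, adjustment alone yields up to 51.6 × 2 = 103 g in either direction. A simulation of the cell r = 0.4, m = +2 (4,000 runs, 40 per group) gave −199 g unadjusted and −293 g adjusted, in line with the formula.

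For scale, the standard error of the unadjusted difference is 500 × √(2/40) = 112 g, so the largest shifts are about one standard error.

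These shifts count as bias where the difference in gain results from hypertension. If it preceded hypertension, the same shift could be a proper removal of confounding. Only the timing of the measurement separates the two, and the protocol leaves it open.

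**3. Gestational age at birth.** Assume an SD of 2 weeks, gain of 0.3 to 0.5 kg per week (rate k) and the same 4.5 kg for the rest. Then g = 4k / (20.25 + 4k²), and a true difference d becomes d − g·k·d. For d = −1 week this gives −0.983 (k = 0.3), −0.969 (k = 0.4) and −0.953 (k = 0.5). The mechanical route therefore shrinks the difference by 2 to 5%. If the rest of the gain also differs by 2 kg between groups, the extra shift at k = 0.4 is (1.6/20.89) × 2 = 0.15 week, in either direction.

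**4. Binary outcomes.** Assumed risks of 5% vs 15%, 10% vs 20% and 10% vs 30% with 40 per group give 8, 12 and 16 events. A model with group and three covariates has four terms, hence 2, 3 and 4 events per term. Unadjusted power is 0.32, 0.24 and 0.61. These outcomes cannot carry much adjustment.

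**5. What the contrast estimates.** Both groups receive OMT. Any adjusted or unadjusted difference is hypertensive versus normotensive, not the treatment relation that the analysis section describes.

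**The case against.** The strongest reply is that a flawed definition is being assumed. The protocol nowhere says that gain is taken to delivery, and because it is recorded at each consultation, gain at entry could be used. Gain before week 20 precedes gestational hypertension and could be a genuine confounder. This stands: the defect is the missing time point, not the variable in every form.

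A reader might infer that the fetus inside the gain seriously biases the birth-weight result. The arithmetic does not support that, since this route alone moves it by about 2 g. A reader might also infer a shift of 40 to 200 g, from 20 to 40 g per kg times 2 to 5 kg of extra fluid. Neither input is in the protocol, the top value pairs both extremes, and the direction is presumed.

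Nor does the protocol offer start of prenatal follow-up as a measure of time at risk. It is a defensible marker of access to care and need not be removed. Nothing shows that the groups enrol at different weeks, as the entry window is common to both. That makes gestational age at enrolment a safeguard rather than a correction of a known imbalance. BMI is likewise a judgement: smoking, diabetes and kidney disease are also collected and also absent from the controls.

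Finally, a model may be set out in a statistical analysis plan that is not shown. That softens the point about tests but does not remove it, because this protocol promises control and names only methods that give none. The two problems are also alternatives in part: if only the named tests are run, nothing is adjusted and the weight-gain bias does not arise.

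**Conclusion.** The point holds in limited form, for secondary outcomes. Weight gain without a time point is a poorly fixed covariate that can bias the group differences in birth weight and gestational age at birth, and the named tests cannot deliver the promised control. For birth weight the distortion is of the order of 100 g either way, about one standard error, but only if gain differs by some 2 kg between groups and correlates with birth weight at about 0.4. At a correlation of 0.2 it is about 60 to 70 g. For gestational age it is a few per cent, plus about 0.15 week if gain differs by 2 kg. Every one of these figures rests on assumed inputs, and the sign cannot be known in advance. The documents do not establish that bias will occur.

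**What to change.** In Secondary Outcome, replace weight gain with gain up to study entry, or drop it. Gain up to entry precedes OMT but not chronic hypertension, so dropping it is the cleaner choice. If it is kept, gestational age at enrolment must be in the same model. Keep maternal age, keep start of prenatal follow-up if wanted, and add gestational age at enrolment and BMI at the start of pregnancy.

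In Data Analysis Methodology, name linear regression for birth weight and gestational age at birth. Report the weight z-score alongside birth weight, to help tell earlier delivery from poorer growth. Leave resuscitation, NICU admission and death as unadjusted relative risks unless events suffice, with the threshold stated beforehand. Say plainly that the result compares hypertensive with normotensive women and is not an effect of OMT.

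The cost is wording and slightly more analysis. BMI and the z-score are already collected, and gestational age at enrolment follows from the date of last menstruation and the entry date. Even with every optional term, the linear model has seven parameters (intercept, group, age, start of care, gestational age at enrolment, BMI, gain to entry), leaving 80 − 7 = 73 residual degrees of freedom.

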**Introduction**

Gestational hypertensive disorders (GHD) are a worldwide public health problem. They affect 6 to 8% of women and are the most common cause of pregnancy-related morbidity and mortality worldwide (1,2). GHD represents the main reason for fetal obituary and neonates with perinatal hypoxia (3,4). In Brazil, according to data from the 7th Brazilian guideline on arterial hypertension, the disease affects 7.5% of pregnancies and about 2% progress to eclampsia (5). The diagnosis of the hypertensive disease is given by the presence of high blood pressure. Systolic (SBP) at 140 mmHg and diastolic (DBP) at 90 mmHg, found in an average of at least two measurements in a period of 15 min (1–3). Gestational hypertensive disorders (GHD) are classified as pre-existing when the pregnant woman already presents a condition hypertensive before pregnancy; gestational hypertension (HG), when it appears during pregnancy and pre-eclampsia (PE). AS DHG usually is associated with other comorbidities such as diabetes, kidney disease, hematological disorders, liver, lung, and neurological pathology (2,3).HG manifests itself from the 20th week of gestation onwards and increases the risk of PE and eclampsia. The latter put the life of the fetus and the mother at risk as they are correlated with stroke and pulmonary edema (PE), which are the significant causes of mortality in this pathology. The HG approach involves changes in lifestyle and eating habits in addition to medication use. At the however, the use of medicines during the gestational period is complex since many of the drugs available go beyond the placental barrier and reach the bloodstream of the embryo, which, as it does not have a fully developed body system, is subject to adverse effects (6). Given this scenario, it is necessary to search for therapeutic alternatives for the treatment of DHG. In recent years, the increased demand for integrative and complementary practices (PIC) in the prevention and treatment of various diseases led the Organization World Health Organization (WHO) asks member states to formulate laws to integrate these practices into their health systems. THE Osteopathy is part of the list of PICs recognized in several countries, including Brazil. Osteopathic manual treatment (BMT) is configured as a non-invasive therapy without the use of drugs, where the professional diagnoses and treats somatic dysfunctions through the hands (6). The disorders treated by osteopathy are cataloged as diseases of the musculoskeletal system (ICD-10, M99.00-09) and identified by the TART parameters (Tenderness, Asymmetry, Range of motion change, Tissue texture change) (7). The importance of increasing research about OMT in pregnant women is due to the need to find safe and effective treatment practices during pregnancy, especially in high-risk pregnancies (8–10).

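### The stated adjustment set for birth outcomes omits diabetes and kidney disease, which the protocol links to hypertension and already records, so the hypertensive versus normotensive contrast is confounded.

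*Protocol*

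**What the plan says.** The Secondary Outcome section of the protocol lists birth weight, gestational age at birth, resuscitation, NICU admission and early or fetal death, and then fixes the adjustment: "These results will be controlled by the beginning of prenatal follow-up, maternal age, and weight gain" (gestational weight gain, as the broken line after it shows).

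The Introduction says of the condition that defines the groups: "AS DHG usually is associated with other comorbidities such as diabetes, kidney disease, hematological disorders, liver, lung, and neurological pathology".

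The Details section lists what is taken from the records. It includes "diabetes, kidney pathologies, chronic respiratory pathologies", and also cardiac and autoimmune disease, "BMI at the beginning of pregnancy", smoking, and numbers of children, pregnancies and births.

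Proposed Methodology describes the groups as "a control group formed by normotensive pregnant women and an exposed group of pregnant women hypertensive", drawn by convenience sampling. Both groups receive osteopathic manipulative treatment (OMT). The Exclusion Criteria remove none of diabetes, kidney disease, high BMI or smoking. Data Analysis Methodology names relative risks and mean differences as measures, and the chi-square and t-tests as methods.

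**The concern.** In an unrandomised, unmatched comparison, any condition that is more common in one group and also affects the newborn enters the group difference unless the analysis deals with it. Here the protocol itself names two such conditions, collects them, and then sets out an adjustment that uses neither. Initial BMI, smoking and parity are also recorded and unused. That they differ between the groups is plausible, but it is an inference and not a statement of the protocol.

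At stake is how the secondary birth outcomes can be read. A difference in birth weight or gestational age could reflect hypertension, the accompanying disease, or both. The direction of the error is not known either: diabetes may raise birth weight, while kidney disease and smoking may lower it.

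**Working it through.** **Step 1. Set the sections side by side.**

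| Variable | Linked to hypertension in the Introduction | Recorded (Details) | In the adjustment set (Secondary Outcome) |
|---|---|---|---|
| Diabetes | yes | yes, onset not specified | no |
| Kidney disease | yes | yes | no |
| Initial BMI | no | yes | no |
| Smoking | no | yes | no |
| Parity | no | yes, as number of births | no |

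Nothing else in the design balances these variables: there is no randomisation, matching or relevant exclusion. The two named tests adjust for nothing, so they do not carry out even the three-variable adjustment.

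**Step 2. Inputs for scale.** The protocol gives only a total of 80 women. It states no group sizes, SD, event rates or prevalences, so there is no figure of its own to reproduce. Assumed here:
- 40 women per group, and a birth-weight SD of 550 g
- diabetes in p1 = 25–40% of hypertensive and p0 = 10–15% of normotensive women
- relative risk r = 1.5–3 of a yes/no outcome, such as NICU admission, with diabetes
- diabetes effect on birth weight of +100 to +200 g

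**Step 3. Spurious relative risk when the groups do not truly differ:** (1 + p1(r − 1)) / (1 + p0(r − 1)).

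| p1 v p0 | r = 1.5 | r = 2 | r = 3 |
|---|---|---|---|
| 25% v 15% | 1.05 | 1.09 | 1.15 |
| 25% v 10% | 1.07 | 1.14 | 1.25 |
| 40% v 15% | 1.12 | 1.22 | 1.38 |
| 40% v 10% | 1.14 | 1.27 | 1.50 |

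Lowest corner: 1.125 / 1.075 = 1.05. Highest corner: 1.8 / 1.2 = 1.50.

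**Step 4. Spurious difference in birth weight:** (p1 − p0) × effect.
- Smallest: (0.25 − 0.15) × 100 g = 10 g
- Largest: (0.40 − 0.10) × 200 g = 60 g
- Standard error: 550 × √(2/40) = 123 g
- The shift is therefore 10/123 = 0.08 to 60/123 = 0.49 standard errors. With a two-sided 5% test and no true difference, the chance of a significant result rises from 5% to between 5.1% and 7.8%.

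If prevalence is the same in both groups, p1 = p0, and the bias is zero in Steps 3 and 4.

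**Step 5. How many covariates 80 women can carry.**
- *Continuous outcomes.* Intercept, group, the three stated covariates, diabetes in three categories (two terms), initial BMI, smoking and parity make 1 + 1 + 3 + 2 + 1 + 1 + 1 = 10 parameters. That leaves 80 − 10 = 70 residual degrees of freedom, against 75 under the stated set.
- *Yes/no outcomes.* At assumed event rates of 5%, 10% and 20% there are 4, 8 and 16 events. At 10%, a model with four terms (group and the three stated covariates) has 8/4 = 2 events per term, and one with eight terms has 8/8 = 1. That is too few for multi-covariate adjustment.

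**The case against.** **The analysis plan may extend the list.** The Secondary Outcome sentence does not say that these are the only covariates, and full lists often sit in a statistical analysis plan. But the protocol is not silent here. It names a set, and a later plan with a different set would have to depart from it.

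**The clinic's intake is described as free of clinical comorbidity.** Proposed Methodology does say this of the prenatal service. It is the strongest counter-evidence, and it makes assumed diabetes prevalences of 25–40% less secure. It is not an eligibility criterion, however, and it sits badly with enrolling hypertensive women. Women on the ward are recruited too, and the protocol still plans to record these diseases.

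**A group comparison of birth outcomes is not spelled out.** The Secondary Purpose asks for a comparison between groups only for maternal-fetal vascularisation. The perinatal aim is worded more loosely. Still, Data Analysis Methodology promises relative risks and mean differences for fetal outcomes, and the only contrast in the design is hypertensive against normotensive women.

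**Kidney disease may follow from chronic hypertension.** This stands. Adjusting for it could remove part of the real group difference, so it belongs in a sensitivity analysis.

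**Stronger readings that a reader might infer, and that the documents do not support:**
- *That the protocol itself ties obesity and smoking to hypertension.* The list in the Introduction contains neither.
- *That each further comorbidity adds to the bias.* Some may act in opposite directions and partly cancel.
- *That everything needed is already recorded.* Diabetes is listed without saying whether it preceded the pregnancy.
- *That a propensity score would rescue the yes/no outcomes.* With so few events it is fragile as well.
- *That fuller adjustment would reveal what OMT does to birth outcomes.* Both groups receive it, so no covariate list can.

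**Conclusion.** The concern holds for the choice of covariates. Followed as written, the plan gives differences in birth weight and gestational age that are confounded by conditions the protocol identifies and records.

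The size cannot be established from the document. For diabetes alone, the assumed inputs give a spurious relative risk of 1.05–1.50 and a birth-weight shift of less than half a standard error. This is a modest to moderate bias of uncertain direction, in secondary outcomes. It does not make those outcomes worthless, and it does not touch the primary blood-pressure outcome. It is worth correcting because the remedy is cheap and the protocol supplies the reason for it.

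**What to change.** Amend the adjustment sentence under Secondary Outcome, and Data Analysis Methodology to match:

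1. For birth weight and gestational age, name a linear model with group, the three stated covariates, and a short prespecified list from the Details section: diabetes (none, pre-existing, gestational), initial BMI, smoking and parity.
2. Repeat each model with kidney disease added, as a sensitivity analysis.
3. For resuscitation, NICU admission and death, drop the claim of adjustment. Report counts and unadjusted relative risks with confidence intervals, labelled descriptive.
4. State that the adjusted contrast compares hypertensive with normotensive women and does not estimate an effect of OMT, since both groups receive it.

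The cost is a protocol amendment, a little analysis work, about five degrees of freedom, slightly wider intervals, and noting diabetes onset from the medical records. The other variables are already on the collection list. Residual confounding by unrecorded factors will remain and should be acknowledged when the results are reported.
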